**3.5. Inclusion**

Children who are 3-5 years old (parents consented) and present on the day of data collection will be included in the study. Children who are free from infections (such as malaria, and tuberculosis) and taking any medication (such as antacids, famotidine and ranitidine, omeprazole, pantoprazole, proton pump inhibitors and calcium supplements) will be included in this study because medication alter the serum concentration and level. Mothers/guardian will be requested to record the health condition suffered by the child in the past 15 days (**see appendix B**)

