**3.5.1 Exclusion criteria**

Children whose parents/guardians did not give consent will be excluded from the study. Children with physical disabilities that would hinder taking anthropometric measurements will be excluded because of lack of equipment to measure height for people with disability.

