***Figure 4: MUAC measuring tape.***

The MUAC is the circumference of the left upper arm that is measured at the mid-point between the tips of the shoulder and elbow. The participant’s left arm will be bent then the researcher will find and mark the mid-point between the two marks. There arm will be hanging straight down, and a MUAC tape will be wrapped around the arm at the midpoint mark. The MUAC will be measured to the nearest 1m (**see Appendix B**) for recording.

1. ***Dietary intake and patterns***

A one day 24-hour recall will be used to collect detailed information about all foods and beverages consumed using the multiple pass method (Steinfeldt *et al*., 2013). Foods will have been consumed in the past 24 hours, most commonly, from midnight to midnight the previous day (**see Appendix C)**. Six daily intervals will be included, namely: breakfast (period up to 09h00), In-between snack (between 09h00 and 12h00), lunch (12h00 to 14h00), In-between snack (14h00 to 18h00), dinner (18h00 to 20h00), and after dinner (after 20h00). Guardian/parents will provide this information. A FFQ will be used to establish food consumption patterns including the *Cucurbita moschata* seeds. A selected pictorial FFQ will be designed for the children to establish if they know and consume the seeds (**see Appendix D**). Preschool menu will also be evaluated at this stage using the 24 hr recall form for recording at least once a week during the implementation of the intervention.

1. ***Biochemical measurements***

Zinc status will be determined by serum zinc concentrations and iron status via haemoglobin, serum ferritin, transferrin receptor and C- reactive protein (CRP) among pre-school children using flame atomic absorption spectrophotometer. The anthropometric status of the preschool children will be assessed by measuring weight and height to calculate the body mass index (BMI).

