**FOOD SYSTEMS INVENTORY**

1. **Place of food purchase**

| **Code** | **Place (yes 1; no 2)** | |
| --- | --- | --- |
| *14*.1 | Local formal shops |  |
| *14*.2 | Spaza shops |  |
| *14*.3 | Shoprite |  |
| *14*.4 | Pick n Pay |  |
| *14*.5 | Spar |  |
| *14*.6 | Boxer |  |
| *14*.7 | USave |  |
| *14*.*8* | Checkers |  |
| *14*.9 | Choppies |  |
| *14*.10 | Game |  |
| *14*.*11* | Street vendors |  |
| *14*.12 | SaveMor |  |
| *14*.13 | OK grocery |  |
| *14*.14 | Pick up wild foods |  |
| *14*.15 | Other |  |

1. **Household food production (plants)**

| **Code** | **Type (yes 1; no 2)** | |
| --- | --- | --- |
| *15*.1 | Garden |  |
| *15*.2 | Orchard/ Fruit tree |  |
| *15*.3 | Field in the Household |  |
| *15*.4 | Fields away from household |  |
| *15*.5 | Small holder farm |  |
| *15*.6 | Large farm |  |
| *15*.7 | **Other** |  |

1. **Places for food storage**

| **Code** | **Type (yes 1; no 2)** | |
| --- | --- | --- |
| *16*.1 | Refrigerator |  |
| *16*.2 | Deep Freezer |  |
| *16*.3 | Dry room storage |  |
| *16*.4 | Cup board |  |
| *16*.5 | Not specific |  |
| *16*.6 | **Other** |  |

1. **Resources for food preparation**

| Code | Type (yes 1; no 2) | |
| --- | --- | --- |
| *17*.1 | Open fire outside |  |
| *17*.2 | Open fire inside |  |
| *17*.3 | Gas stove |  |
| *17*.4 | Paraffin stove (primus) |  |
| *17*.5 | Electric stove |  |
| *17*.6 | Coal stove |  |
| *17*.7 | Gel stove |  |
| *17*.*11* | Microwave |  |
| *17*.12 | Wonder box |  |
| *17*.13 | Other |  |

| **SECTION B: RECORD SHEET** |
| --- |

1. Name of the preschool……………………………………………
2. Child’s ID…………………………………………….
3. (ii.) Date of Birth……………… day………. Month………………year
4. (iii.) Age………………………….
5. Gender:

| 1 | 2 |
| --- | --- |
| Female | Male |

1. Did the child receive Deworming?

| 1 | 2 |
| --- | --- |
| Yes | No |

1. (a) Body weight……………………………… kg

(b) Body weight…………………………… kg

© Average weight…………………………….. kg

1. (a) Height………………………………. cm

(b) Height………………………………. cm

© Average height……………………………. cm

1. (a) MUAC ………………………………… cm

(b) MUAC………………………………… cm

© Average MUAC …………………. Cm

27 Was the faeces of the collected?

| 1 | 2 |
| --- | --- |
| Yes | No |

28.Temperature of the participants……………………………………

29.Has your child suffered from any health conditions in the last 15 days?

…………………………………………………………………………………………………………………………………………………………………………………………

30.Does the child have a Road to Health Booklet (RtHB)?

| Yes | No |
| --- | --- |

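### The inclusion sentence in section 3.5 contradicts its own reason on medication, and the exclusion list does not settle which meaning applies

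*Protocol*

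**What the plan says.** Section 3.5 (Inclusion) has two operative sentences. The first admits children aged 3 to 5 whose parents have consented and who are present on the day of data collection. The second concerns health and medication. It describes "Children who are free from infections (such as malaria, and tuberculosis) and taking any medication", gives examples of the medication ("such as antacids, famotidine and ranitidine, omeprazole, pantoprazole, proton pump inhibitors and calcium supplements"), and concludes that these children "will be included in this study because medication alter the serum concentration and level". The section then points to Appendix B, where the caregiver reports the child's recent health conditions.

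Section 3.5.1 (Exclusion criteria) has two entries: "Children whose parents/guardians did not give consent will be excluded from the study" and "Children with physical disabilities that would hinder taking anthropometric measurements will be excluded". It mentions neither medication nor infection.

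The measurements exposed to this rule carry the primary aim. Under biochemical measurements in 3.6.2.5: "Zinc status will be determined by serum zinc concentrations and iron status via haemoglobin, serum ferritin, transferrin receptor and C- reactive protein (CRP)".

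**The concern.** An eligibility rule should follow from its stated reason. Here the reason is that medication changes the serum measurements, which is an argument for keeping medicated children out, while the sentence says they are included. No other visible part of the protocol resolves the conflict.

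The protocol's main aim is to show a change in zinc and iron status, and it names the affected medicines itself, so no outside source is needed to see the relevance. Preschools are randomised as whole units (3.4 and 3.6.3.3), and several people take part in recruitment and data collection: Table 3.6 gives recruitment to preschool teachers or principals and questionnaires to fieldworkers. If one site reads the sentence as admitting medicated children and another as barring them, the difference falls by preschool and could differ between arms. If medication use is not recorded at enrolment, it cannot readily be sorted out or adjusted for afterwards.

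**Working it through.** The point rests on the text. The protocol states no figure on it, so there is nothing to reproduce.

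**1. The two ways to read the sentence**

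| | Reading A: plain | Reading B: free from governs both items |
|---|---|---|
| Condition on infection | Child has none | Child has none |
| Condition on medication | Child is taking it | Child is not taking it |
| Fits the stated reason? | No; the reason argues the other way | Yes |
| Fits the word *any*? | Awkwardly | Yes; it is the usual word after a negative |
| Stated outright in the text? | It is the plain reading | No; it must be inferred |

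Reading B is probably what was meant. Reading A is what the sentence says on its face.

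**2. Whether another provision settles it**

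- First sentence of 3.5: age, consent and presence only. It admits medicated and unmedicated children alike.
- Section 3.5.1: consent and physical disability only. It removes no child on account of medication.
- Appendix B, item 29: "Has your child suffered from any health conditions in the last 15 days" asks about conditions, not medicines. The morbidity checklist that follows also has no medication line in the visible text. Part of Appendix B was removed from the copy available for review, so a medication item may exist there.

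Nothing visible chooses between A and B.

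**3. Illustration of scale**

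The planned total is 436 (section 3.4). The share of children on the listed medicines is not given. Assuming 1% to 10%:

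- 436 × 0.01 = 4.36, about 4 children
- 436 × 0.10 = 43.6, about 44 children

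Nothing in the documents supports either end of this range. It shows scale only.

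**4. How far an arm mean could move**

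The feeding-trial schematic in 3.6.3 estimates 73 children per preschool. Three preschools per arm (section 3.4) give 3 × 73 = 219; four per arm (the schematic) give 4 × 73 = 292. Suppose 5 children in one preschool were each shifted by one full standard deviation (both figures assumed):

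- 5 / 219 = 0.023 SD
- 5 / 292 = 0.017 SD

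With 7 children, about 10% of one preschool, 7 / 219 = 0.032 SD. Under these assumptions the shift is small.

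**The case against.** The strongest reply is that the sentence is clumsy rather than wrong. Reading B is grammatically available, *any* fits it, and the reason makes sense only that way. Fieldworkers are nutritionists trained by the researcher, with methods standardised during piloting (section 3.7), so the intended meaning may well reach the sites. The design compares change from baseline with a randomised control, so a medication effect that was stable across both visits would largely cancel.

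Most of this stands. It supports calling the text ambiguous and the likely effect small. It does not remove the defect: the probable intent is not written down, the plain reading is the opposite, and the cancellation argument assumes that each child's medication use stays the same over six months.

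A reader might also infer three stronger things that the documents do not support:

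- *That medication use is a requirement for entry.* Reading A taken strictly would enrol only medicated children. That is hard to square with the first sentence of 3.5 or with finding 436 children in six to eight preschools, so it is unlikely to be applied.
- *That a few medicated children in one preschool could noticeably move an arm mean.* The arithmetic above gives about 0.02 to 0.03 SD even with a one-SD shift per child.
- *That the data form has no medication field.* Only the visible part can be checked.

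Finally, once the inclusion sentence is clear, repeating it under 3.5.1 is partly duplication. What matters is that the two sections agree.

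**Conclusion.** The concern holds as a contradiction within an operative eligibility rule. On its plain reading, section 3.5 admits children on medicines that it says alter the serum measurements, and 3.5.1 does not remove them. The sentence is best described as ambiguous and at odds with its own reason, most likely through a lost negation; it is not shown to be a deliberate or unmistakable reversal.

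What is at stake is inconsistent enrolment across randomised preschools and some avoidable noise or imbalance in serum zinc and iron. The size cannot be computed from the documents because neither the prevalence of medication use nor its effect on the assays is given. It is probably small. The 4 to 44 children are an illustration under an assumed 1% to 10%, and the conclusion does not depend on them.

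Eligibility belongs in the protocol, so this is not a detail to leave to a statistical analysis plan. It should be corrected before enrolment.

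**What to change.** 1. Reconcile the second sentence of 3.5 with its stated reason, so that only one reading is possible. If exclusion is what was meant, it could require that the child is free from infections and is not taking any of the listed medications.
2. Make 3.5.1 consistent with the corrected sentence. A cross-reference is enough if the inclusion wording is unambiguous.
3. Confirm that Appendix B records current medication use. If it does not, add one yes/no item beside the 15-day health question.

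The cost is one sentence, one consistency check in 3.5.1 and at most one form item. The downside is that a few children may become ineligible.

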**3.5.1 Exclusion criteria**

Children whose parents/guardians did not give consent will be excluded from the study. Children with physical disabilities that would hinder taking anthropometric measurements will be excluded because of lack of equipment to measure height for people with disability.

***3.6. DATA COLLECTION PROCEDURE***

The study will be conducted in four phases: phase one: development of intervention, phase two: baseline survey, phase three: implementation of the Intervention, and phase four: post intervention survey as depicted in Figure 1. The sections below provide details for each phase.

**3.6.1.** **PHASE ONE: DEVELOPMENT AND PILOTING OF THE INTERVENTION**

**3.6.1.1. Aim:** To develop the intervention consisting of *Cucurbita Moschata* snack and nutrition education.

**3.6.1.2. Objectives**

3.6.1.2.1. Develop *Cucurbita moschata* dish.

3.6.1.2.2. Develop a nutrition education lesson on the importance of *Cucurbita moschata seeds.*

3.6.1.2.3. Testing the microbial activity, toxicity level, micronutrient content (bioavailability of Fe, and Zn), shelve life, nutrient stability and the presence of iron and zinc inhibiters using standardized methods.

**3.6.1.3. Study design**

The design for this phase will be experimental and observation for the development of recipes and a qualitative approach for development of the song, following Homophonic parallelism (good lyrics, harmonies and melodies).

**3.6.1.4. Recipe Development and Preparation**

Four (4) recipes will be developed during using standardization cycle adopted from Spears and Gregoire (2010). The steps to be followed will be recipe formulation, product evaluation, quantity adjustment, and sensory evaluation. The process is illustrated below.

**Figure 3:** Recipe Standardization Cycle Adopted from (Spears & Gregoire, 2010)

The recipe development and sensory evaluation will be conducted in the food science laboratory at the University of Venda. The sensory evaluation will help standardize the recipes. This will be followed by testing the microbial activity in a microbiology laboratory at the University of Venda. In addition, toxicity, micronutrient content, life span and nutrient stability will be tested in a food science laboratory. The presence of iron and zinc inhibiters in the recipes will be evaluated in the food science laboratory at the CSIR and Central Analytical Facilities (CAF) in Stellenbosch University using standardized methods.

The recipes will be tested for total plate count microbial activity in accordance with codex principles of Hazard Analysis Critical Control Point (HACCP). Recipes will be examined for a specific pathogen or its toxins (such as coliform- for hygiene, yeast, moulds and fungi) (Khalaf and Raizada, 2016). This examination will detect organisms that may be indicative of the possible presence of pathogens or to detect the presence of specific spoilage organisms. Testing for microbial activity of the recipes is vital to assure that critical raw materials are satisfactory for their intended use.

***3.6.1.5. Cucurbita moschata seeds dishes***
[figure not shown]

***(a) Grounded Cucurbita moschata seeds mixed cooked flesh and sugar***

After the seeds are removed from *Cucurbita moschata,* they will be rinsed with water to remove any strings and bits of squash. The seeds will be patted dry and placed in a small bowl. Once the seeds are dried they will be grounded in a machine until they form a powder*. The skin of Cucurbita moschata* will be peeled off and the flesh will be chopped into cubes, chopped flesh of *Cucurbita moschata* will be cooked with 2 cups of water and 30g of sugar. The cooked *Cucurbita moschata* will be mixed with the powder (grounded seeds) to make a paste.

**(b)** ***Paste mixed with cinnamon***

The cooked *Cucurbita moschata* will be mixed with the powder (grounded seeds) to make a paste. Cinnamon will be added to paste to enhance flavour and taste.

**(c) *Paste mixed with vanilla essence and honey.***

Vanilla essence and honey in the food increase the appearance, flavour and taste. The same procedures as in (a) will be followed, except that the sugar will be replaced with honey.

**(d) *Paste cooked with butter***

Butter also known to add flavour and taste to food. Fats assist in the absorption of vitamins. Same procedure as in (a) above.

**(e) Sensory evaluation procedure using hedonic scale**

Children below five years are not considered able to express differences in taste perception by use of the preferential methods. A child’s own spontaneous verbal judgement will be used to estimate the difference; preference and acceptability of the recipe using the hedonic scale **(see Appendix A).** The children will select the most liked or preferred dish from the four dishes, then the researcher will rank them accordingly according to “most liked by children”. Two will be used for this intervention to allow for variety.

**3.6.1.6.** **Development of the nutrition education song on the consumption of *Cucurbita moschata***

The design will follow Homophonic parallelism (Boamah, 2012) in composing the song. Harmonic parallelism is the harmonizing of a single melody or subordinate melody and moving with it in parallel. This means the notes that harmonize the melody follow its characteristic shape and rhythm and this type of parallelism is common to all African peoples. The researcher will lead the composition of the song along with the children during piloting.

The lyrics as spelled out below have been determined. The lyrics will be repeated in three languages (English, *Xitsonga* and *Tshivenda)*

1. *We love butternut x2 (Chorus) 3. Ri funa mafhuri (Chorus)*

*We eat seeds x2 Rila na thanga x2*

*And we get zinc, iron dzi rinea pfushi x2*

*We eat seeds Rila thanga x2*

*We eat seeds.*

1. *Hi randza makwembe x2 (Chorus)*

*Ma kahle ka hina x2*

*Hi dya tinghwembe ta kona hi kula*

*Hi kula kahle*

*Hi van a matimba x2*

1. *Thanga dza fhuri (Chorus)*

*ndi zwavhudi u dzila x2*

*dzi rinea pfushi x2*

*kha dzi liwe x2*

Harmonies and rhythms will be tested and practised with the children until an acceptable tune is reached. The acceptable rhythm will be recorded, so that it can be used in the preschools during the intervention. Six to ten tapes will be made for each preschool and to keep extras in the event of damage or loss.

**3.6.1.7.** **Piloting of the intervention and training package.**

The song and the recipes will be pre-tested and piloted using the University of Venda preschool children for a week. The participants will form part of informal sensory evaluation panel during the recipe standardization. The song also will be tested with the children. Permission to use the preschool will be sought from the University and the parents, mostly University employees.

**3.6.1.8. Outcome of phase one**

The outcome will be developed recipes with microbial activity, toxicity level, micronutrient content analysis and identified inhibitors. Two most liked recipes will be selected. The dosage of the Zn and Fe will be determined as well as the portion size and the frequency of supplementation required. The song is composed and recorded for use later.

**3.6.2. PHASE TWO: BASELINE SURVEY.**

**3.6.2.1. Aim:** The aim will be to recruit, and screen potential participants and collect baseline data.

**3.6.2.2. Objectives:**

3.6.2.2.1. To determine the demographic and environmental factors of the participants.

3.6.2.2.2. To measure the anthropometry of the study participants (Weight, Height, MUAC)

3.6.2.2.3. Determine the dietary diversity scores of participants using 24- hour recall

- - - - 1. Determine dietary patterns of the study participants using FFQ.
        2. To determine serum zinc concentrations among pre-school children using flame atomic absorption spectrophotometer before consuming *Cucurbita moschata* seeds.
        3. To determine the iron status of pre-school children using hemoglobin, serum ferritin, transferrin receptor and C- reactive protein (CRP) before consuming the *Cucurbita moschata* (butternut) seeds.

**3.6.2.3. Design:** The study design will be a cross sectional survey in which the researcher will measure the demographic and environmental factors, anthropometries, diet patterns, zinc and iron status of pre-school children. A cross sectional study is a method that involve observation of a population or a representative subset at one specific point in time (Leedy and Ormrod, 2010). All measurements parameters will be done at one point using a quantitative approach.

**3.6.2.4. Participants recruitment**

The researcher will recruit study participants from the randomly selected preschools form the two purposefully selected municipalities of the Vhembe district.

***Visit 1:***

A list of pre-schools will be obtained from the district office and preschools from Musina and Collins Chabane will be randomly selected. The selected preschools will be visited, and the research aims, and objectives will be explained to the headmaster. In addition, permission to include pre-schools in the sample will be requested.

***Visit 2:***

A parents’ meeting will be arranged. The researcher will provide explanation to parents who need clarity before giving consent for children to participate in the study. A list of children whose parents will consent will be generated.

**Visit 3 and 4**

Arrangements for data collection will be made with the pre-school management. A full day or two will be required for each preschool and space for data collection will be requested form the preschool management.

The baseline survey will thus require four visits per preschool (visit 1: 2 days; visit 2: 6 days; visit 3 and 4: 12 days) for a total of 20 days.

**3.6.2.5. Measurements**

The following measurements will be carried out during the baseline survey: demographic and environmental factors, anthropometrics, dietary intakes and patterns, and biochemical parameter.

1. ***Physical arrangements***

A separate classroom will be requested to be used to ensure privacy for the children and their parents. Two stations will be arranged; (1) measurements of anthropometrics and interviews, and (2) collection of blood samples.

1. ***Demographic and environmental factors***

In this study, demographic factors will be collected, such as age, gender and socioeconomic status. Environmental factors will include the abiotic (temperature, amount of sunlight, and pH of the water) and the biotic (disease, competition, parasitism, and dietary consumption). A validated questionnaire will be used (**see Appendix B**). Since children are under five, mothers will be requested to provide this information.

1. ***Anthropometrics measurements***

Anthropometrics will include weight, height and mid upper arm circumference will be used to assess nutritional status. The weight and height will be taken twice, and average computed to reduce error.

